## Abstract

**Background:**

One relevant strategy to prevent the onset and progression of type 2 diabetes mellitus (T2DM) focuses on increasing physical activity. The use of activity trackers by patients could enable objective measurement of their regular physical activity in daily life and promote physical activity through the use of a tracker-based intervention. This trial aims to answer three research questions: (1) Is the use of activity trackers suitable for longitudinal assessment of physical activity in everyday life? (2) Does the use of a tracker-based intervention lead to sustainable improvements in the physical activity of healthy individuals and in people with T2DM? (3) Does the accompanying digital motivational intervention lead to sustainable improvements in physical activity for participants using the tracker-based device?

**Methods:**

The planned study is a randomized controlled trial focused on 1642 participants with and without T2DM for 9 months with regard to their physical activity behavior. Subjects allocated to an intervention group will wear an activity tracker. Half of the subjects in the intervention group will also receive an additional digital motivational intervention. Subjects allocated to the control group will not receive any intervention. The primary outcome is the amount of moderate and vigorous physical activity in minutes and the number of steps per week measured continuously with the activity tracker and assessed by questionnaires at four time points. Secondary endpoints are medical parameters measured at the same four time points. The collected data will be analyzed using inferential statistics and explorative data-mining techniques.

**Discussion:**

The trial uses an interdisciplinary approach with a team including sports psychologists, sports scientists, health scientists, health care professionals, physicians, and computer scientists. It also involves the processing and analysis of large amounts of data collected with activity trackers. These factors represent particular strengths as well as challenges in the study.

**Trial Registration:**

The trial is registered at the World Health Organization International Clinical Trials Registry Platform via the German Clinical Studies Trial Register (DRKS), DRKS00027064. Registered on 11 November 2021.

## Administrative information

Note: the numbers in curly brackets in this protocol refer to SPIRIT checklist item numbers. The order of the items has been modified to group similar items (see http://www.equator-network.org/reporting-guidelines/spirit-2013-statement-defining-standard-protocol-items-for-clinical-trials/).

## Introduction

### Background and rationale {6a}

Type 2 diabetes mellitus (T2DM), which results in elevated blood sugar levels (hyperglycemia) due to insulin resistance, is one of the most common chronic diseases among adults [1]. Hyperglycemia and diabetes mellitus are associated with micro- and macrovascular disorders such as coronary heart disease, stroke, renal and eye disease, as well as an increased risk of developing certain types of cancer and depressive symptoms [2–4]. Genetic predisposition, age, and lifestyle factors, such as a sedentary lifestyle, an unhealthy diet, and smoking, are associated with a higher risk of developing T2DM [5–7]. Therefore, one relevant strategy to prevent the onset of the disease in healthy individuals and to slow or halt disease progression and the development of secondary diseases in people with T2DM focuses on increasing physical activity [8–13].

Studies suggest that physical activity can reduce fasting blood glucose (FBG) and average blood sugar concentrations (measured by glycated hemoglobin (HbA_1c_)) in healthy individuals [14–16]. These reductions could lower the risk of hyperglycemia and thus the risk of developing T2DM [15]. According to the results of a meta-analysis, compliance with the World Health Organization (WHO) recommendation to be physically active at a moderate level of intensity for at least 150 min per week would result on average in an FGB reduction of 4.13 mg/dL and 0.21% lower HbA_1c_ in healthy individuals [14]. In addition, the results of Cavero-Redondo et al. found that engaging in more than 150 min of physical activity per week could lead to a greater reduction in HbA_1c_ levels compared with having lower levels of physical activity [16].

Research also suggests that physical activity can reduce FBG and HbA_1c_ levels in people with T2DM or pre-diabetes [11, 14, 17, 18]. Based on the previously mentioned meta-analysis, following the WHO recommendation for moderate physical activity for at least 150 min a week would result on average in an FBG reduction of 7.07 mg/dL and 0.24% lower HbA_1c_ in people with T2DM or pre-diabetes [14]. In addition, large-scale cohort studies have shown that physical activity significantly reduces the risk of mortality [11].

Physical activity can be increased not only through structured programs, such as aerobic or resistance training, but also through unstructured leisure time physical activity [13]. Valid, representative, and objectively measured data are needed to understand the complex factors affecting physical activity in individuals’ daily routines [19]. Activity trackers are promising tools for objectively collecting physical activity data and increasing physical activity in different target populations [20–25]. They are built into consumer electronics (so-called wearables), such as smartphones, smartwatches, and fitness bracelets, and regularly collect physical activity data during everyday life; the processed data are then reported to the end-user [26].

Several studies from different countries show promising results regarding the use of activity trackers:

Baskerville et al. conducted a meta-analysis based on 12 randomized controlled trials or controlled trials ((R)CTs) using pedometers and accelerometers (in combination with behavioral interventions in some studies) that suggested that these interventions could lead to a statistical significant increase in physical activity of about 1 hour per week and a statistically significant reduction in HbA_1c_ levels of about 0.1 mmol/mol in T2DM patients [27]. However, no statistically significant effects were found regarding changes in blood pressure, body mass index (BMI), and lipid values [27].

The meta-analyses conducted by Gal et al. based on 18 randomized controlled trials (RCTs) and by Brickwood et al. based on 12 (R)CTs, in which activity tracker-based consumer electronics in combination with behavioral interventions were used, indicate a statistically significant increase in steps (standardized mean difference (SMD): 0.67 and 0.23) as well as in moderate to vigorous physical activity per day (SMD: 0.49 and 0.28) [20, 28]. However, with the use of the wearable intervention alone, the study results of Brickwood et al. only suggested a statistically significant increase in steps (SMD: 0.20; mean difference (MD): 475 steps per day) but not in moderate to vigorous physical activity per day (SMD: 0.17; MD: 40 min per day) [20].

The effectiveness of activity tracker-based interventions in everyday life could be influenced by user behavior, user satisfaction, perceived effectiveness and usefulness of the technology, and technology acceptance in general [29, 30]. Furthermore, the validity and reliability of the data collected by activity trackers could be affected by technical problems associated with the device, changes made to the device (e.g., software updates), and incorrect use of the device by the person using it or by the study personnel [31]. A systematic review conducted by Bort-Roig et al. reported that the accuracy of physical activity data (steps per day) measured with smartphones ranged from 52 to 100% [21]. Regarding the accuracy of fitness trackers, a systematic review of Fitbit devices suggested an overall tendency to underestimate steps (MD: − 9%) [32].

In previous studies in which activity trackers were used to monitor and enhance physical activity, several limitations were mentioned, including small sample sizes, short study durations, lack of standardized analytical procedures, and further research needs, such as the use of tracker interventions in subjects with T2DM [20, 26–28, 33–36]. Therefore, a RCT with a longer study duration and larger sample size relative to former studies will be conducted to investigate the effectiveness of an activity tracker-based intervention alone and in combination with a behavioral intervention. Healthy individuals, individuals with pre-diabetes and individuals with T2DM will be included in the study to assess the benefits of the intervention regarding risk reduction for the development of T2DM onset as well as disease progression. The aim of this trial is to answer the following research questions: (1) Is the use of activity trackers suitable for longitudinal assessment of physical activity in everyday life? (2) Does the use of a tracker-based intervention lead to sustainable improvements in the physical activity of healthy individuals and in people with T2DM? (3) Does the accompanying digital motivational intervention lead to sustainable improvements in physical activity for participants using the tracker-based device?

### Objectives {7}

In this trial, it is hypothesized that the moderate and vigorous physical activity of the participants in the groups (no diabetes, diabetes and pre-diabetes) with activity tracker increases statistically significantly in terms of the target values at the 5% level of significance over time (at baseline (*t*_0_), after 3 months (*t*_1_), after 6 months (*t*_2_) and after 9 months follow-up (*t*_3_)). The measurements of moderate and vigorous physical activity with questionnaire are hypothesized to be statistically significantly different at the 5% level of significance from the measurements of physical activity with the activity tracker. In addition, an explorative hypothesis is tested: The moderate and vigorous physical activity in minutes per week measured with the activity tracker of participants in the different intervention groups (tracker-based intervention alone or tracker-based intervention combined with digital motivational intervention) increases differently over time.

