## Statistical methods

### Statistical methods for primary and secondary outcomes {20a}

Visual and descriptive (pre-)analyses will be undertaken. All statistical data analyses will be performed with the statistical software R [68]. The primary outcomes (moderate and vigorous physical activity in minutes and steps per week) will be analyzed regarding changes in the percentage of participants that meet the WHO recommendations to be physically active. Therefore, descriptive and explorative time-series analyses will be performed [76]. The overall physical activity as well as the amount of physical activity for different groups will be compared between measurements with the activity tracker and the questionnaire (the BSA-F [54] module) both in minutes per week at t_2_ (post-treatment) using the Bland-Altman method [77].

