Since comparisons between participants in the intervention and control groups as well as comparisons of participants at different time points take place, a linear mixed model with two levels will be calculated to test the primary hypotheses [78]. The dependent variable is moderate and vigorous physical activity per week measured with a questionnaire. In the linear mixed model, time (*t*_0_ to *t*_3_) is the intra-class factor, and grouping (intervention group with tracker-based device, intervention group with tracker-based device and digital behavior intervention, and control group) is the inter-class factor [78]. The covariates psychosocial factors, socio-demographic factors, physical and mental health, comorbidities, alcohol and tobacco consumption, nutritional awareness, usage behavior and user satisfaction (with regard to the activity tracker and app), diabetes disease and treatment, participation in external interventions, and severity of the disease are assessed as categorical variables. Random intercepts are assumed while all other effects are regarded as fixed. The null model will be calculated and compared with alternative models regarding its fit via Akaike and Bayesian information criterion [78, 79]. Further, interactions will be considered and will be included in the model if the explanatory power of the model is strengthened. The same analysis will be performed for the assessment of secondary endpoints. Effects of all analyses will be considered significant if *p* < 0.05. All assumptions of the statistical tests will be checked in advance graphically and by appropriate tests. Bonferroni correction will be applied to counteract the problem of multiple testing [80].

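### No test is specified for the explorative hypothesis on tracker-measured activity between the two tracker arms; the only model that separates them uses questionnaire data.

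*Protocol article*

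**What the plan says.** Background and rationale {6a} lists three research questions. The third reads: "Does the accompanying digital motivational intervention lead to sustainable improvements in physical activity for participants using the tracker-based device". Objectives {7} turns it into a hypothesis, introduced by "In addition, an explorative hypothesis is tested". The outcome is "The moderate and vigorous physical activity in minutes per week measured with the activity tracker of participants in the different intervention groups", and the claim is that the two arms (tracker alone, tracker plus digital motivational intervention) change differently over time.

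Statistical methods {20a} says that "a linear mixed model with two levels will be calculated to test the primary hypotheses". In that model "grouping (intervention group with tracker-based device, intervention group with tracker-based device and digital behavior intervention, and control group) is the inter-class factor", so the two tracker arms are separate levels. The outcome is explicit: "The dependent variable is moderate and vigorous physical activity per week measured with a questionnaire". On interactions, the section says that "interactions will be considered and will be included in the model if the explanatory power of the model is strengthened".

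The same section uses tracker data in two ways. One concerns the share of participants who meet the WHO activity recommendation, for which "descriptive and explorative time-series analyses will be performed". The other is a Bland-Altman comparison of tracker and questionnaire at t2.

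**The concern.** Objectives {7} announces a test on one instrument, and the analysis section supplies a model on another. This comparison does not have the difficulty of the main one. The control group has no device, so intervention against control has to rely on questionnaires. Between the two tracker arms, both sides wear the device, and Concealment mechanism {16b} shows that both are filled by sealed-envelope allocation.

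If the plan is followed as written, the only specified inferential contrast for research question 3 rests on self-report. Who will be blinded {17a} states that subjects cannot be blinded, and Intervention description {11a} gives one of the two arms a goal-setting function for activity, which could influence how activity is reported. The device data that the hypothesis names would not be used to compare the arms. The article itself argues, in the Introduction and the Discussion, that objectively measured activity data are needed.

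**Working it through.** The check is mainly textual: does any section specify a test that meets all three parts of the hypothesis (tracker minutes, the two tracker arms, a difference in change over time)?

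| Place | Outcome | Separates the two tracker arms? | Difference in change over time? |
|---|---|---|---|
| {7}, explorative hypothesis | tracker minutes per week | yes | yes |
| {20a}, mixed model | questionnaire activity per week | yes | only if an interaction improves the model |
| {20a}, same analysis for secondary endpoints | medical parameters, as defined in Outcomes {12} | yes | as above |
| {20a}, time-series work | share meeting the WHO recommendation | not stated | descriptive and explorative |
| {20a}, Bland-Altman | tracker against questionnaire at t2 | groups mentioned, no arm contrast | no |
| {12}, closing statement | listed outcomes | intervention against control only | between time points |
| {20b}, subgroups | primary outcomes | disease status only | not stated |

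No row below the first meets all three parts.

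**Are the data planned?** Participant timeline {13} (text with Fig. 1) has the device measuring continuously for 6 months in the intervention group and makes wear optional from then until t3. Trial design {8} gives 1:1 allocation and splits the intervention group 50:50. With 1642 participants and 15% drop-out from Sample size {14}:

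- randomised per tracker arm: 1642 / 4 = 410.5
- after drop-out: 410.5 × 0.85 = 348.9, about 349
- difference detectable with 80% power, two-sided 5%, single time point: 2.80 × √(2/349) = 0.21 SD

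**Would tracker data be more precise?** Assume equally correlated values and a common standardised scale. The variance of a mean of k values is r + (1 − r)/k. Adjusting for one baseline value with the same correlation subtracts r². The detectable difference is 2.80 × √(2 × variance/349). The protocol gives r = 0.33 between visits; r = 0.7 is my alternative, because weekly tracker values may be correlated differently.

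| Summary | Variance, r = 0.33 | Detectable | Variance, r = 0.7 | Detectable |
|---|---|---|---|---|
| Tracker, mean of 26 weeks | 0.33 + 0.67/26 = 0.356 | 0.13 SD | 0.712 | 0.18 SD |
| Tracker, mean of 4 weeks | 0.33 + 0.67/4 = 0.498 | 0.15 SD | 0.775 | 0.19 SD |
| Questionnaire, mean of t1 to t3 adjusted for t0 | 0.553 − 0.109 = 0.444 | 0.14 SD | 0.80 − 0.49 = 0.31 | 0.12 SD |

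The ordering depends on the averaging window and the correlation. The tracker rows carry no baseline adjustment, because the correlation between tracker values and the t0 questionnaire is not given. Precision is therefore not an argument for the change.

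**The case against.** The strongest reply is that the mixed model in {20a} says it serves the primary hypotheses. It needs questionnaire data because the control group has no tracker, and it does not claim to test the explorative hypothesis. Explanation for the choice of comparators {6b} also says the two tracker groups are compared, and the exact model for an explorative question may stand in a document not shown. This stands in part. A reader might infer that the hypothesis will never be tested; the article does not support that, because its explorative time-series work could touch tracker data. What it supports is that no test is specified. The gap is still more than condensation: {20a} names an outcome for the only model separating these arms, and it is not the outcome in {7}.

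A reader might also see a firm conflict of status, since {6a} lists the question among three while {7} calls it explorative. That is weak. A listed question may be answered by an explorative hypothesis, and a three-level group factor does not make the add-on contrast primary.

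Nor does it follow that the instruments would give opposite answers. Objectives {7} expects tracker and questionnaire readings to differ, but a difference between instruments need not alter the contrast between arms.

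Finally, tracker data have weaknesses of their own. Strategies to improve adherence {11c} sets no further control of wear, {20c} fills missing values from neighbouring data, and goal setting may itself change wear. This stands, and is a reason to report both instruments.

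**Conclusion.** The point holds in limited form. The article announces a test of tracker-measured weekly minutes between the two tracker arms and specifies none. The only inferential model that separates these arms uses self-report, and the arm-by-time term that the hypothesis requires is left to model fit. The consequence is confined to one explorative comparison of about 349 against 349 participants; the primary comparison with the control group is not affected.

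The conclusion rests on the article's wording, not on a calculation. The arm size assumes that 1642 are recruited, the stated split and 15% drop-out. The benefit of a change is that the analysis matches the stated hypothesis and does not depend on self-report alone.

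**What to change.** In {20a}, add an explorative mixed model of weekly tracker minutes of moderate and vigorous activity, restricted to the two randomised tracker arms and to the planned 6-month wear period (t0 to t2). Include arm, time and an arm-by-time term that is prespecified and kept whatever the fit criteria say. Adjust for disease stratum and t0 questionnaire activity; the article describes no tracker measurement before allocation, so the questionnaire is the available baseline. Report the arm term together with the interaction, because an effect present from the first weeks would appear in the former.

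Beside it, report the questionnaire contrast between the same two arms from the existing mixed model, including t3. Tracker wear is voluntary after t2, so any statement about sustained effects at t3 has to rest mainly on the questionnaire. State in both {7} and {20a} that the add-on comparison is explorative.

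The cost is one further model on data already planned, plus a few sentences. The drawback is that the tracker analysis depends on wear, which may differ by arm, so wear time should be reported by arm.

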### Trial design {8}

The monocentric, pragmatic RCT has a parallel group design with an allocation ratio of 1:1. Tests of equivalence will be performed to compare the intervention group wearing a smartwatch with an activity tracker in everyday life with the control group that does not wear the device. Furthermore, 50% of the participants in the intervention group will also receive a digital motivational intervention via a smartphone app. The planning and implementation of the study is orientated towards the Declaration of Helsinki [37].

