### Sample size {14}

The sample size was calculated according to the primary hypothesis. The correlation between the results of the different measurement times is estimated to be 0.33 based on similar studies [66]. Regarding the effect size, the results of similar studies show that a medium effect can be assumed, which is why the effect size is estimated at *d*=0.5 and *f*^2^=0.15 [27, 28, 33, 66]. A dropout rate of 15% is derived from one of these studies [66]. For a power (1-β) of 0.8 with a significance level of *α*=0.05, assuming an effect size of *f*^2^=0.15, an adjustment with design effect, and a drop-out rate of 15%, a sample size of at least 1642 participants is necessary. With the help of the results of the pre-studies, a more precise calculation of the sample size is possible and the sample size can be adjusted if necessary.

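### The trial design item announces equivalence tests between the arms while the aim, sizing and model are for superiority; secondarily, the tracker-questionnaire hypothesis of difference does not match the planned agreement analysis

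*Protocol article*

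**What the plan says.** All places are in the protocol article.

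**Comparison of the arms**
- Trial design {8}: "Tests of equivalence will be performed to compare the intervention group wearing a smartwatch" with controls who wear no device.
- Background and rationale {6a}, research question 2: "Does the use of a tracker-based intervention lead to sustainable improvements in the physical activity of healthy individuals and in people with T2DM".
- Objectives {7}: activity in the tracker groups "increases statistically significantly in terms of the target values at the 5% level of significance over time". An explorative hypothesis compares the two tracker groups with each other. No hypothesis sets intervention against control.
- Sample size {14}: "the effect size is estimated at *d*=0.5 and *f*^2^=0.15", with power 0.8, alpha 0.05, 15% dropout and a design effect whose value is not printed, giving at least 1642 participants.
- Statistical methods {20a}: "a linear mixed model with two levels will be calculated to test the primary hypotheses", with time (t0 to t3) and a three-level group factor. The decision rule is "Effects of all analyses will be considered significant if *p* < 0.05". Sidedness is not stated.

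**Tracker against questionnaire**
- Objectives {7}: the questionnaire measurements are expected to be "statistically significantly different at the 5% level of significance from the measurements of physical activity with the activity tracker". No time point is named.
- Statistical methods {20a}: the two are compared "both in minutes per week at t_2_ (post-treatment) using the Bland-Altman method".
- Research question 1 asks whether trackers are suitable for longitudinal assessment.

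**The concern.** An equivalence test takes a relevant difference as its null hypothesis. Rejecting that null means concluding that tracker and control do not differ by more than a margin, which is the opposite of what research question 2 hopes to show. {8} is the only item that names the type of test between the arms. {20a} names a model and a p-value threshold, and {7} speaks only of change within the tracker groups. The article therefore leaves two incompatible readings of the main between-arm inference. A superiority result that misses significance could later be presented as equivalence under {8}, with a margin picked after the data are seen.

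The tracker-questionnaire comparison has a smaller problem of the same kind. Whether two instruments differ significantly depends heavily on the number of pairs and does not answer whether they agree, and one time point informs little about agreement over time.

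**Working it through.** **The plan's own figure.** The aim is to see what kind of test 1642 comes from.
- d = 0.5, two-sided 0.05, power 0.8: n per arm = 2 × (1.96 + 0.8416)² / 0.5² = 63, so 126 in total and 149 after dividing by 0.85. With an assumed design effect 1 + (m − 1) × 0.33 for m = 2, 3 or 4 (1.33, 1.66, 1.99), the totals are 198, 248 and 296.
- f² = 0.15 with 1 to 50 predictors (noncentral F): 55 to 238. With design effect 1.99 and dropout: 129 to 558.
- Neither reaches 1642 without a multiplier that the article does not state. Reading 0.15 as a standardised mean difference, with no design effect, gives 1396, and 1396 / 0.85 = 1642.4. That is an inference and not the stated calculation.

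All these routes are difference tests, and {14} describes nothing based on an equivalence margin. The failure to reproduce 1642 is a separate matter and does not affect this point.

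**What an equivalence test would do.** Evaluable per arm: 1642 × 0.85 / 2 = 697.85, taken as 697. SE of the standardised difference = √(2/697) = 0.0536. Two one-sided tests at 0.05 each, normal approximation:

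P(equivalence) = Φ((M − δ)/SE − 1.645) − Φ((−M − δ)/SE + 1.645)

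The margins M are assumed, because none is given.

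| Margin (SD) | True δ = 0.5 | True δ = 0.2 | True δ = 0 |
|---|---|---|---|
| 0.2 | 0% | 5% | 96% |
| 0.3 | 0% | 59% | >99.9% |
| 0.4 | 0.02% | 98% | 100% |
| 0.5 | 5% | 100% | 100% |
| 0.6 | 59% | 100% | 100% |

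At M = 0.4 and δ = 0.5: (0.4 − 0.5)/0.0536 = −1.867; −1.867 − 1.645 = −3.512; Φ = 0.0002. The δ = 0.2 column shows why an unstated margin matters: the same true effect gives 5% or 98% depending on whether the margin is 0.2 or 0.4 SD.

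If equivalence were really meant, the total for 80% power at δ = 0 would be 2 × 2 × ((1.645 + 1.2816)/M)² / 0.85, rounding up n per arm first: 4031, 1793, 1010, 648 or 163 for M = 0.10, 0.15, 0.20, 0.25 or 0.50.

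**What superiority would do with the same N.** Power = Φ(δ/SE − 1.96): above 99.9% at 0.5 SD, 96.2% at 0.2 SD and 80.0% at 0.15 SD.

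**Tracker against questionnaire.** Pairs: half of 1642 wear the device, so 821 × 0.85 ≈ 697.
- Observed mean difference that just reaches p < 0.05: 1.96/√697 = 0.074 SD of the paired differences. A true bias of that size would be detected with only about 50% power.
- True bias detected with 80% power: (1.96 + 0.8416)/√697 = 0.106 SD.
- 95% CI half-width of each limit of agreement: 1.96 × √(1/697 + 1.96²/(2 × 696)) = 0.127 SD.

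The same data therefore estimate the limits of agreement closely, whichever way the significance test falls.

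**The case against.** The strongest reply is that one sentence in {8} should not be taken as controlling. {20a} says which model tests the primary hypotheses, and it looks for effects. A reader might infer from {8} that the trial will in fact be run and analysed as an equivalence trial; the documents do not support that, because nothing in {6a}, {7}, {14} or {20a} follows through on it. An article may also leave a margin to the full protocol or analysis plan, so its absence alone is no defect. Both points stand. What remains is the contradiction in a stated test framework, which {20a} does not settle because it names no between-arm framework and {7} has no hypothesis against control.

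A reader might also infer that agreement is to be judged by a difference test at one time point. No section says so: {7} states a difference hypothesis without a time point, and {20a} names t2 but uses Bland-Altman, an agreement method that also estimates bias. Expecting self-report to differ from a device is a legitimate hypothesis, and {7} does not tie it to research question 1. Nor does that question rest on t2 alone: {20a} plans time-series analyses, {11a} a validation study against reference accelerometers (n = 30) and a one-week usability pre-study (n = 25), and usability and later use are asked about at 6 and 9 months. This half therefore reduces to a mismatch between {7} and {20a} and the restriction to t2.

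Finally, the SD of the paired differences is not given, so a bias of 0.11 SD cannot be called trivial in minutes per week. That is correct, and the argument does not need it.

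**Conclusion.** The equivalence sentence in {8} contradicts the aim, the hypothesis, the sizing and the model. Under the planned d = 0.5, an equivalence test would succeed about 0.02% of the time at a 0.4 SD margin and 5% at 0.5 SD, and success would argue against the intervention. This is a wrongly stated framework that should be corrected; it does not show that the sample size or the planned model is wrong.

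The tracker-questionnaire point is secondary. The hypothesis in {7} fits neither the Bland-Altman analysis in {20a} nor research question 1, and agreement is examined only at t2.

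Assumptions: 15% dropout spread equally over the arms; the two tracker groups pooled against control; a single between-arm comparison with a normal approximation, no covariates, no design effect and no Bonferroni correction; assumed equivalence margins; and a valid pair from every retained wearer. Fewer valid pairs or a corrected alpha would raise the 0.11 SD figure but would not turn a significance test into evidence on agreement.

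**What to change.** - **{8}:** replace the equivalence sentence with a superiority comparison of intervention versus control, two-sided at 5%, tested through the group-by-time effect of the mixed model in {20a}. Name the contrast (tracker groups combined against control). {20a} now admits interactions only if they strengthen the model, so state that this one is always included.
- **{7}:** add the matching intervention-versus-control hypothesis. Editing {8} alone would leave {7} with an increase over time in the tracker groups only.
- **{7} and {20a}, instruments:** restate the tracker-questionnaire hypothesis as estimation of mean bias and limits of agreement with confidence intervals. Extend the planned Bland-Altman analysis to t1 and t2, allowing for repeated pairs from the same person. Report t3 descriptively only, because wear after six months is voluntary and those pairs would be self-selected.

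Cost: wording in three items. N does not change, and no new data are needed, since questionnaires run at all four time points and the tracker records continuously for the first six months. Recruitment had already begun in January 2022, so the change belongs in a dated formal amendment made before outcomes are compared by arm.
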